### Randomization

The biostatistician (WS) will generate the random allocation sequence; all other research team members will not have access to the randomization sequence. Schools in each cohort will be randomized (1:1:1) to one of three parallel arms (*n* = 14 schools per arm): 1) RUBIES + HELM; 2) RUBIES only; 3) or educator psychoeducation. Randomization will be stratified based on median split for: 1) size of school at the time of enrollment; and 2) number of possible dyads (identified at screening for each enrollment cohort). Study enrollment, randomization, and engagement for all schools begins in the Spring prior to Year 1. Schools randomized to psychoeducation will be enrolled in the trial for one year; schools randomized to either RUBIES + HELM or RUBIES only will be enrolled in the trial for two years; children will be enrolled for one year.

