## Clinical interventions

### Rubies

RUBIES is a manualized, 9-session educator-delivered intervention that addresses externalizing behaviors in autistic children [45, 46]. Although RUBIES follows a standardized manual, behavioral strategies are tailored to the autistic student, informed by target behaviors and their hypothesized function, as well as child- and educator-specific classroom needs. One goal of RUBIES is for educators to build mastery over a set of behavioral skills that are used to support the student currently under their care with potential to generalize to other autistic students in their classrooms. RUBIES also focuses on engaging the student’s broader educational team through an initial collaborative planning session as well as targeted goals in every session focused on activating a weekly team communication and generalization plan. Sixteen weeks will be allotted to complete the 9 modules, to account for cancellations, scheduling conflicts, holidays, etc. Educators will receive a RUBIES workbook, access to an online platform that houses resources (e.g., extra copies of activity sheets, video models of an educator implementing RUBIES strategies), and a toolkit with recommended sensory tools and premade visual supports to accompany RUBIES use. Educators will engage in RUBIES sessions with a coach who has a master’s degree or higher and completed training to fidelity in RUBIES (i.e., manual review, viewing of RUBIES sessions, co-leading sessions with a certified RUBIES-trainer). The coach will facilitate weekly hour-long RUBIES sessions with educators via Zoom at a convenient time. Coaching sessions will include a practice plan review, didactic instruction on behavioral strategies, and coaching and consultation to tailor newly learned strategies. Educators will be offered a Booster session at three time points during Year 02. Booster sessions will involve reviewing three main components of RUBIES: conducting a functional assessment, prevention strategies, and how to implement more effective responses to challenging behaviors.

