### Educator psychoeducation

Autistic children in schools assigned to the educator psychoeducation condition will receive standard of care school-based interventions (no research intervention). Participating educators in schools randomized to this condition will receive an online, self-paced webinar program via a web-based learning portal. The program includes 8-modules on supporting autistic children in schools, without discussion of behavioral management strategies: 1) Introduction to Autism, 2) Autism in Schools, 3) Interventions for Supporting Communication, 4) Executive Functioning, 5) Inclusion in Schools, 6) Autism EBPs, 7) Social Functioning in Autism, and 8) Recess Engagement Strategies. Each module is 20–35-min long.

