### Implementation strategies

#### HELM

Members of the research team will work with school principals and district-level leaders who participate in HELM over the course of 9 months [33]. HELM includes eight components: 1) Assessment and Feedback. Principals, assistant principals, and educators familiar with RUBIES will complete an initial 360º survey on RUBIES implementation leadership and climate in the spring semester prior to the year of enrollment (HELM baseline, Year 0), Weeks 16, 24, 52, and 76. A detailed feedback report will be shared with the leader, to create a personal leadership development plan to support implementation and sustainment; 2) Initial Training. Principals, assistant principals, and district leaders will participate in didactic and interactive trainings on developing strategic implementation leadership behavior and an EBP implementation climate in their schools in the summer prior to Year 01 of study enrollment; 3) Leadership Development Plan. Principals will work with their coach to review their 360º assessment data and develop goals for improving implementation leadership and climate during the initial training and during coaching; 4) Individual Coaching. A former principal will provide monthly 1-h one-on-one coaching sessions via Zoom with the principals and assistant principals to review progress and update the leadership development plan. 5) Group Coaching. A former principal will offer optional monthly 1-h group coaching calls with HELM principals to review progress and share strategies across schools; 6) Organizational Strategy Meeting. Two, 1-h meetings with principals and district-level leaders will be held in each semester of Year 01, to develop and update an organizational implementation strategy plan. This meeting will provide a structured discussion of alignment between school- and district-level efforts to support RUBIES implementation and sustainment; 7) Professional Learning Collaboratives. Two professional learning collaboratives will be held with principals in Year 01 to review content (align HELM strategies with principles from the National Educational Leadership Standards, and EBP sustainment) and share strategies; and 8) Graduation. Principals’ final feedback will be reviewed, progress for the past year will be celebrated, and sustainment plans will be reviewed.

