#### Implementation outcomes

Sustainment (primary implementation outcome) is defined as the level of educator fidelity to RUBIES through the second year of study enrollment (Weeks 52 and 76). Fidelity to RUBIES is operationalized on the RUBIES Educator Behavior Support Plan Implementation (BSPI) measure which will be rated by a trained independent evaluator masked to study condition. The BSPI is designed to assesses the educator’s current implementation of strategies that are detailed on the Behavior Support Plan, which is an organizing document that captures all RUBIES strategies developed for the educator’s student in collaboration with the RUBIES coach and implemented by the educator in Year 1. The IE rating on the BSPI will be completed at Weeks 16, 24, 52, and 76 and will be based on discussion with the educator around their current implementation of RUBIES strategies documented on their behavior support plan. Ratings on the BSPI are based on a scale of 1–8 (1 “none of the components of the behavior support plan are being implemented”; 4 “behavior support plan is partially implemented and with some implementation errors”; 8 “the behavior support plan is implemented consistently as intended in its entirety”). In a prior study of RUBIES, BSPI scores of educators randomized to RUBIES averaged 6.78 (SD = 1.25; scale of 1–8) [21].

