### Aim 1 analyses

Aim 1 evaluates the main effect of RUBIES vs. educator psychoeducation on child externalizing behavior among children in Year 1 of study enrollment. The primary outcome for this comparison is change in child externalizing behavior from baseline to Week 24, contrasting all groups assigned to RUBIES vs. educator psychoeducation (i.e., arms 1 & 2 vs. arm 3). We will fit a three-level Linear Mixed Model (LMM) as follows: the Level 1 model (piece wise time) with a “knot” (i.e., inflection point) at Week 16 used to capture each child’s change in externalizing behavior from Baseline to Week 16, and potentially different slope from Week 16 to Week 24. At Level 2 (child/educator; due to 1:1 pairing), each growth parameter will be modeled as a function of an intercept and child/educator-level covariates. We will select covariates by testing for differences across arms on youth and educator characteristics; covariates will be included if the effect size ≥|0.2|. At Level 3 (school), we will include a random intercept to account for the nesting of the child-educator dyads within schools and a treatment assignment indicator ([RUBIES + HELM] + [RUBIES only] vs. educator psychoeducation). We will test the interaction effect of treatment condition with time. Linear combinations of the growth parameters from this model will be used to test whether improvement in child externalizing behavior was superior for autistic children assigned to [RUBIES + HELM] + [RUBIES only] vs. educator psychoeducation from Baseline to Week 24.

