### Aim 2 analyses

Aim 2 compares the effect of HELM vs. educator coaching on RUBIES sustainment as measured by BSPI scores (arm 1 vs. arm 2). The hypothesis states that intervening with HELM will induce better sustainment (i.e., higher RUBIES fidelity) in Year 2 at Week 52 and Week 76 compared to educator coaching only. The two observations of sustainment for each educator (paired 1:1 with a child) in Year 2 are nested within the educator, who is nested within a school. For this outcome, we will fit an LMM with the following hierarchical structure: the Level 1 model (observation) will include Week 52 and Week 76 fidelity observations for each educator. This level does not include a growth model because we do not assume fidelity will systematically increase or decrease during the sustainment school year; instead, we assume random fluctuation around an educator mean for the year. At Level 2 (educator), we will include a random intercept and educator-level covariates such as years of experience which may be a potential confounder. Covariates will be selected as described above. At Level 3 (school), we will include a random intercept and a treatment assignment indicator (RUBIES + HELM vs. RUBIES only) which will be contrast coded to facilitate main effect interpretations. The coefficient for the treatment assignment indicator in this model will test whether RUBIES sustainment (i.e., level of RUBIES fidelity in the second year of study enrollment) was superior for educators assigned to RUBIES + HELM compared to educators assigned to RUBIES only at Week 52 and Week 76. As a secondary implementation outcome, we will analyze a binary indicator of RUBIES sustainment at Week 52 and Week 76 (based on the CGI-S) to evaluate whether HELM improved the odds of sustaining RUBIES at a provisional ‘sustainment’ cutoff. This analysis will use a similar model as Aim 2, but data from different timepoints or distributions (LMM and Generalized LMM for binary outcomes).

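### Neither primary model has a term for the RUBIES coach: Aim 1 standard errors are too small if coaches share schools and differ in effect, and Aim 2 is confounded if coaches are unbalanced between arms 1 and 2

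*Protocol article*

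**What the plan says.** The Aim 1 analyses section states "We will fit a three-level Linear Mixed Model (LMM) as follows" and then lists the levels: time, child/educator, school. At the school level "we will include a random intercept to account for the nesting of the child-educator dyads within schools", together with the treatment indicator. The Aim 2 analyses section lists observation, educator and school: "At Level 3 (school), we will include a random intercept and a treatment assignment indicator (RUBIES + HELM vs. RUBIES only"). The Sample size and power section allows for clustering within schools and for no other clustering.

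On delivery, the Rubies section says "The coach will facilitate weekly hour-long RUBIES sessions with educators via Zoom at a convenient time". The Educator psychoeducation section says that arm 3 educators "will receive an online, self-paced webinar program via a web-based learning portal", so arm 3 has no coach. The Implementation outcomes section says that the plan rated by the BSPI is developed "in collaboration with the RUBIES coach and implemented by the educator in Year 1". The Randomization section says "Schools in each cohort will be randomized (1:1:1) to one of three parallel arms", with 14 schools per arm. The number of coaches, their caseloads, and whether one coach works in both RUBIES arms are not given.

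**The concern.** Coaching is remote, so a coach is not tied to one school. Unless each of the 28 RUBIES schools has its own coach, dyads in different schools share a coach. Their outcomes are then correlated if coaches differ in effect. The written models treat schools as independent of one another.

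The two aims are exposed differently. In Aim 1 the coach exists on one side of the contrast only (a partially nested design), so coach variance adds to the uncertainty of the RUBIES mean and is missing from the standard error. In Aim 2 both arms have coaches, and what matters is who works where. If the coaches in arm 1 are different people from those in arm 2, the HELM contrast contains the difference between two sets of coaches. The BSPI is directly open to this, because the coach helps write the plan that it scores. If coaches are completely separate by arm, no analysis of the trial data can reliably separate the two effects, so this has to be handled in the design.

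**Working it through.** **Inputs from the Sample size and power section.** Aim 1: 84 vs 42 children, SD 6.2, within-person correlation 0.3, school ICC 0.10, 3 dyads per school, 20% attrition, difference 3.8, 80% power. Aim 2: 42 vs 42 educators, SD 0.17, 10% for school clustering, 25% attrition, difference 0.13, 80% power. A two-sided 5% level is assumed.

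**Assumed, because the article gives neither.** Coach ICC (ρ) 0.01 to 0.10, and 2 to 14 coaches across arms 1 and 2.

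**Step 1: reproduce the stated power.** The design effect is 1 + (3 − 1) × 0.10 = 1.2.
- Aim 1: variance = 6.2² × (1 − 0.3²) × 1.2 × (1/33.6 + 1/67.2) = 1.874, SE 1.369. Power = Φ(3.8/1.369 − 1.96) = 79.3%.
- Aim 2, with one rating per educator: variance = 0.17² × 1.2 × 2/31.5 = 0.002202, SE 0.0469. Power = Φ(0.13/0.0469 − 1.96) = 79.1%.

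Both stated powers come back with school clustering alone, so no coach variance is budgeted.

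**Step 2: Aim 1 with K coaches shared by arms 1 and 2.** Added variance = ρ × 6.2²/K. For ρ = 0.05 and K = 6 this is 0.320, and the true variance is 1.874 + 0.320 = 2.194. The SE ratio is √(2.194/1.874) = 1.08. Actual type I error = 2 × (1 − Φ(1.96/1.082)) = 7.0%. Power with a correct SE is 72.8%. Without the 0.3² adjustment the type I error is 6.8%. The SD cancels from the ratio, so the outcome scale does not affect the type I error.

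Results at ρ = 0.05:

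| Coaches | SE ratio | Type I, formula | Type I, school-mean simulation | Type I, change-score simulation |
|---|---|---|---|---|
| 2 | 1.23 | 11.1% | 10.8% | 12.5% |
| 6 | 1.08 | 7.0% | 6.7% | 7.5% |
| 14 | 1.04 | 5.9% | 4.8% | 5.5% |

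The last column lets the coach act on change, which a school random intercept cannot absorb. School-level variation in change is set to zero there to isolate the coach. Over the whole assumed range the formula gives 5.2% (ρ = 0.01, 14 coaches) to 16.8% (ρ = 0.10, 2 coaches).

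**Step 3: Aim 2 with k coaches per arm, completely separate by arm.** Added variance = 2 × ρ × 0.17²/k. For ρ = 0.05 and k = 3 this is 0.000963, and the true variance is 0.003165. The SE ratio is 1.20, the type I error 10.2%, and power with a correct SE 63.7%. If the two Year 2 ratings are averaged (variance factor (1 + 0.3)/2 = 0.65), the type I error is 13.0%.

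Results at ρ = 0.05:

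| Coaches per arm | Type I, formula | Type I, simulation |
|---|---|---|
| 1 | 19.7% | 22.5% |
| 2 | 12.8% | 13.5% |
| 3 | 10.2% | 10.1% |
| 7 | 7.2% | 6.3% |

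Over the whole assumed range the formula gives 5.4% to 30.3%.

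**Step 4: Aim 2 with the same coaches balanced over both arms.** Coach effects cancel from the contrast. Simulated type I error is 4.0% to 4.4% at ρ = 0.05, and 3.0% to 4.8% for ρ from 0.02 to 0.10. Leaving coach out then makes the test slightly conservative.

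**The case against.** A condensed article commonly leaves coach numbers and caseloads to the full protocol, and a balanced assignment rule may exist there. The Rubies section describes one coaching program for both RUBIES arms and nothing suggests separate staff. It also uses a standardized manual and coaches trained to fidelity, which should limit coach differences. With about 14 coaches the inflation is negligible, and with one coach per school the coach effect would be part of the school effect. The variance formulas are also only approximations to the mixed models in the plan.

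Most of this stands. A reader might infer that the Aim 1 standard errors are certainly too small, or that a HELM effect in this trial would really be a coach effect. The documents support neither. The first needs non-zero coach variance and coaches who each serve several schools. The second needs coaches unbalanced between arms 1 and 2, and the article does not say that they are.

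The stated structure remains open to criticism. The article writes out every level of both models, so the missing coach term is part of the stated model and is more than a detail left for later. A manual limits coach variance without excluding it, since strategies are tailored to each student and the plan is written jointly. Formula and simulation agree closely enough for an order of magnitude.

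**Conclusion.** The point holds conditionally. Both primary models stop at the school, although a coach delivers RUBIES in arms 1 and 2 only and shapes the plan behind the Aim 2 score.

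- **Aim 1:** modest inflation if coaches are few and differ in effect, about 7% at an assumed ICC of 0.05 with 6 coaches, and close to 5% with about 14.
- **Aim 2:** the larger risk, but only if coaches are not balanced between arms 1 and 2. At ICC 0.05 with 3 separate coaches per arm, type I error is about 10%. Balanced coaches give no inflation.

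These figures rest on two inputs that the article does not give, and they show scale only. The HELM coach is a further person-level source, in arm 1 only: "A former principal will provide monthly 1-h one-on-one coaching sessions via Zoom with the principals and assistant principals". The Aim 2 model does not represent that source either, and it is not in these figures. The change is worth making now because, according to the Discussion, no participants had been enrolled as of February 2026.

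**What to change.** 1. **Design, before cohort 1.** State the number of RUBIES coaches. Have each one serve both arm 1 and arm 2 schools, balanced as closely as school numbers allow across cohorts, and record the coach for every dyad. Exact equality within a cohort may be impossible: about 14 schools over three arms leaves 4 or 5 per arm, too few for six coaches each to hold equal, non-zero numbers in both. Over three cohorts there are 14 schools per arm, so near-balance is feasible.
2. **Aim 2.** Add coach as a factor crossed with arm, so that arms are compared within coach.
3. **Aim 1.** Add a coach random effect that is active only in the RUBIES arms and acts on change (coach by time), with small-sample degrees of freedom. A coach intercept alone would largely drop out of the change contrast and leave the test uncorrected. If there are too few coaches to estimate the variance, report a sensitivity analysis over plausible coach ICCs.

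**Cost.** An assignment rule, one recorded field and a few sentences of analysis text. The Aim 1 interval widens somewhat if coach variance is real (power 72.8% against 79.3% in the 6-coach case), and the coach variance is imprecise when coaches are few. There is also a trade-off: fewer coaches are easier to balance over arms 1 and 2, but they raise the coach contribution in Aim 1, which is proportional to 1/K.

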### Sample size and power

The primary focus of Aim 1 is to test the main effect of RUBIES (RUBIES + HELM and RUBIES only) vs. educator psychoeducation on change in children’s externalizing behavior from Baseline to Week 24. Assuming a Type-I error rate of 5% and SD of 6.2, a conservative within-person correlation in externalizing behavior of r = 0.3, 10% intraclass correlation (clustering within schools) for variance inflation and 20% attrition rate in children, a total of 126 autistic children paired 1:1 with educators (84 autistic children for RUBIES + HELM and RUBIES only vs. 42 children in educator psychoeducation) nested within 42 schools are needed to detect a difference of at least 3.8 points in the comparison of slopes in ABC-I with 80% power. A difference of 3.8 corresponds to a moderate standardized effect size of d = 0.62 in between groups change in children’s externalizing behavior and this effect size is clinically meaningful based on prior research [16]. The study assumed a modest clustering within schools of 10% because of the 1:1 pairing of the educator and autistic child. We expect 3 child-educator dyads per school to consent and enroll in the study. Hence, a total of 126/3 = 42 schools are needed.

For Aim 2, we will use only educators in the RUBIES + HELM vs. RUBIES only (84 educators within 28 schools) arms. With 84 educators as the effective sample size (42 each), nested within 28 schools, we have 80% power to detect a difference of at least 0.13 (or d = 0.76) in RUBIES sustainment (Week 52 and Week 76) between RUBIES + HELM vs. RUBIES only assuming SD = 0.17 based on pilot RUBIES data, a Type-I error rate of 0.05, 10% variance inflation for clustering within school effect, 25% attrition rate and within-person correlation of observations = 0.3. We assumed a higher attrition rate for educators since the turnover rate for educators are higher post pandemic.

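### The Aim 1 model tests raw change with a separate baseline per arm, but the stated 80% power for 3.8 points, with all its listed inputs, fits a baseline-adjusted analysis

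*Protocol article*

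**What the plan says.** Under Aim 1 analyses, the primary clinical outcome is change in externalizing behavior from baseline to Week 24, arms 1 and 2 against arm 3. The mixed model has piecewise time with a knot at Week 16, a random school intercept, a treatment indicator and a treatment-by-time interaction. The test is described as follows: "Linear combinations of the growth parameters from this model will be used to test whether improvement in child externalizing behavior was superior". Neither a common baseline mean nor adjustment for the baseline score is stated. Other covariates enter only if the arms differ on them by an effect size of at least 0.2.

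Under Sample size and power, the Aim 1 calculation takes an SD of 6.2 and a 5% type I error. For correlation and clustering it gives "a conservative within-person correlation in externalizing behavior of r = 0.3, 10% intraclass correlation (clustering within schools) for variance inflation". Attrition is put at 20%. The numbers compared are "84 autistic children for RUBIES + HELM and RUBIES only vs. 42 children in educator psychoeducation". On cluster size: "We expect 3 child-educator dyads per school to consent and enroll in the study". The claim is 80% power for a difference of 3.8 points on the ABC-I. The standardized size is given thus: "A difference of 3.8 corresponds to a moderate standardized effect size of d = 0.62 in between groups change".

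**The concern.** Three visits with a knot at the middle one give a saturated mean structure, so the baseline-to-Week-24 combination equals the difference in mean change between arms. Because the treatment indicator lets baseline differ by arm, the variance of that contrast carries a factor 2(1 − r). At r = 0.3 this is 1.4 times the single-visit variance. An analysis adjusted for baseline carries 1 − r² = 0.91.

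The stated 3.8 points does not appear to include the factor 1.4. If it does not, the 80% belongs to a different analysis from the one planned for the primary clinical hypothesis, and the planned analysis gives up precision that the already collected baseline could supply.

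**Working it through.** **Inputs** (Sample size and power): 84 vs 42 children; 20% attrition, so 67.2 vs 33.6; SD 6.2; r = 0.3; ICC 0.10; 3 dyads per school. The design effect (DE) is 1 + (3 − 1) × 0.10 = 1.2. Sidedness is not stated; two-sided 5% is assumed.

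**Formulas.**
- √(1/67.2 + 1/33.6) = 0.2113
- SE = 6.2 × √(factor × DE) × 0.2113
- Detectable difference at 80% power = (1.960 + 0.842) × SE
- Power at 3.8 = Φ(3.8/SE − 1.960)

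**Reproducing the plan's figure.**
- Baseline-adjusted, factor 0.91, DE 1.2: SE = 1.369, detectable difference 3.84 (d = 0.62), power 79%. This uses every listed input.
- Factor 1 with a flat 1.1 inflation: SE = 1.374, detectable difference 3.85 (d = 0.62), power 79%. This leaves r unused. It can be read as a Week 24 comparison with a single-visit SD, or as a change analysis with 6.2 as the SD of change.

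**The planned change analysis.**

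| Reading of SD 6.2 | Clustering | Factor × DE | SE | Detectable difference | Power at 3.8 |
|---|---|---|---|---|---|
| Single visit | ICC inflates variance of change, DE 1.2 | 1.4 × 1.2 | 1.698 | 4.76 | 61% |
| Single visit | No penalty | 1.4 × 1.0 | 1.550 | 4.34 | 69% |
| SD of change | DE 1.2 | 1.0 × 1.2 | 1.435 | 4.02 | 75% |
| SD of change | Flat 1.1 | 1.0 × 1.1 | 1.374 | 3.85 | 79% |
| SD of change | No penalty | 1.0 × 1.0 | 1.310 | 3.67 | 83% |

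A generalized least squares check of the three-visit model, with free baselines and dropouts' baseline scores kept, gives 62.5% when the clustering acts at each visit. It gives 72.0% when clustering is only a constant school intercept.

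**Does adjustment ever lose precision?** 2(1 − r) − (1 − r²) = (1 − r)², which is positive for every r below 1. So for a given single-visit SD the adjusted variance is always the smaller. At r = 0.3 the ratio is 1.4/0.91 = 1.54: the change analysis would need about 54% more children for the same precision.

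**The case against.** The strongest reply is that 6.2 may be the SD of change. The effect size is expressed as a between-group difference in change, and the Aim 2 power text speaks of a 10% variance inflation. With a flat 1.1 the planned analysis then reproduces 3.85 points and 79%. This reading stands as possible. Against it, r would have no role, although the article lists it and calls it conservative, and an ICC of 0.10 with 3 dyads per school implies 1.2, not 1.1.

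Second, the stated model has only a random intercept for school, and a constant school intercept cancels from within-child change. This is right. With a single-visit SD it moves the figure to 69–72%, still below 80%.

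Third, r = 0.3 may be too low. With DE 1.2 and a single-visit SD, raw change reaches 80% at r of about 0.55, so the size of the shortfall depends on r. The adjusted analysis has about 89% there, so its advantage remains.

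Fourth, free baselines have a rationale. Schools are randomized in the spring before Year 1. Educators then identify the child, and they rate baseline after the dyad consents, with the clinical baseline in the fall. Randomization therefore does not guarantee equal baseline means among the enrolled children. This stands against a constrained-baseline model as the primary analysis. It does not stand against using the baseline score as a covariate, provided the change model is kept alongside it.

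A reader might infer that the power is simply 61%, or that 3.8 points cannot be obtained from the planned analysis. The documents support neither, because the SD is undefined and the way the ICC enters is not stated.

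**Conclusion.** The concern holds as a mismatch between two stated parts of the plan. The Aim 1 model tests raw change with arm-specific baselines, while the power statement with all its listed inputs corresponds to a baseline-adjusted test. Power for the planned test at 3.8 points is about 61–72% if 6.2 is a single-visit SD and 75–83% if it is the SD of change. The upper end needs the SD-of-change reading with no clustering penalty.

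These figures assume a two-sided 5% test, 20% attrition and r = 0.3 where r is used. They are for the ABC-I, a secondary outcome. They carry over to the SESBI-R, the primary outcome, only on the standardized scale (3.8/6.2 = 0.61), so they do not establish the power for the SESBI-R itself. The gain from adjusting for baseline does not depend on settling these points.

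**What to change.** 1. **Aim 1 analyses.** Pre-specify the baseline score of the outcome (SESBI-R for the primary) as a covariate in a mixed model of Weeks 16 and 24. Keep the school random effect and test the Week 24 treatment contrast.
2. **Baseline means.** Do not constrain them to be equal across arms in the primary model. Keep the planned piecewise change model as a sensitivity analysis. Neither model removes bias from selection or rating after randomization, but disagreement between them would show that the conclusion depends on how baseline is handled.
3. **Sample size and power.** State whether 6.2 is a single-visit SD or an SD of change, and how r and the ICC enter. Use 1 + (3 − 1) × 0.10 = 1.2, and restate the power for the model actually used.

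The cost is changed model wording and a recomputed power line, with no new data or participants. The estimand becomes the baseline-adjusted Week 24 difference and should be described so. The article reports no enrollment as of February 2026, so on that status the change can precede any outcome data.
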